| **Protocol Treatment** | [figure not shown]  The principal investigator (or designated surgeon) will perform surgery (mini-plate or suture-anchor) according to the allocation results. Surgery will be performed by an orthopedic surgeon experienced in cervical laminoplasty. The surgical method and pre- and postoperative evaluation schedule are as follows.  **【Surgical Method】**  Under general anesthesia, a midline longitudinal skin incision is made from C2 to C7 in the prone position. Dissection is performed up to the medial facet joints. A double-door laminoplasty is performed on the laminae of C3-6, enlarging 2-4 laminae.  Dome-shaped laminectomy of C2 and C7 is added as needed.  ＜Control Group＞ Mini-Plate  Screws are placed in the expanded laminae at C3-6, and a plate is applied. Screw and plate sizes are determined according to the lamina shape in each case.  ＜Experimental Treatment Group＞ Suture-Anchor  An anchor is placed in the lateral mass at any level from C3-6. Sutures are applied to the ligamentum flavum and sutured to maintain the expanded position.  **[Pre- and Postoperative Evaluation Schedule]**  1) Pre-operative: X-ray, CT, MRI, clinical evaluation  2) Postoperative 1 week: CT  3) Postoperative 1 year: X-ray, CT, MRI, clinical evaluation, direct medical costs  4) Postoperative 2 years: X-ray, CT, MRI, clinical evaluation, direct medical costs |
| **Target Study Population** | 216cases |
| **Research Period** | Total Research Period: October 17, 2025 (jRCT Publication Date) to March 31, 2031 (5.5 years)  (Planned Registration Period: 3 years, Follow-up Period: 2 years after registration completion, Analysis Period: 0.5 years) |
| **Number of Research Facilities** | 3 facilities (Institute of Science Tokyo Hospital, Saiseikai Kawaguchi General Hospital, Saku Medical Center) |

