(4) ～(6)　The JOA score is a physician-led assessment of spinal cord symptoms originating from the cervical spine. Patient-reported outcomes such as EQ-5D, VAS, and NDI were set as secondary endpoints. Furthermore, EQ-5D will also be used as the utility value when calculating the incremental cost-effectiveness ratio.

(7) For safety assessment, the retention rate^7)^ (Figure 4), an objective indicator for enlarged lamina reclosure, was set as a secondary endpoint.

[figure not shown]

(8) As a safety endpoint, the proportion of hinge fractures in enlarged laminar segments on CT^8)^ was set as a secondary endpoint.

(9) As an endpoint for surgical goal achievement, the proportion of hinge fractures showing bone union on CT was set as a secondary endpoint.

(10) Postoperative cervical kyphotic deformity is a morphological change that leads to recurrence of spinal cord symptoms and poor outcomes in cervical laminoplasty^7-9)^. As indicators of kyphotic deformity, the C2-7 lordotic angle and C-SVA were set as secondary endpoints, along with the C7 slope as a factor influencing these (Figure 5).

[figure not shown]

(11) Reduction in the cross-sectional area of the paraspinal muscles (Fig. 6), which are cervical extensors, has been reported as a factor influencing occipital pain^20)^ and as a factor involved in post-laminoplasty reclosure^7)^. Therefore, the postoperative paraspinal muscle area at the C4-5 level was set as a secondary endpoint.

[figure not shown]

(12)(13) Post-laminectomy membrane, caused by posterior dural scarring after laminectomy, is considered a factor in spinal cord re-compression^21)^. However, its incidence rate across different laminoplasty techniques remains unclear. Postoperative dural canal area and the Grading of the mass posterior to the dural sac ^22)^ (Figure 7) were set as secondary endpoints to evaluate spinal cord re-compression.

[figure not shown]

(14) A key objective of this study is to demonstrate that the experimental treatment (suture- anchor) is non-inferior in efficacy and safety to the control treatment (mini-plate), while being less expensive and offering superior cost-effectiveness. As an indicator for comparing the cost-effectiveness between the experimental and control groups, the commonly used measure, ICER, was set as a secondary endpoint.

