**7.2****Observation/Examination Items and Schedule**

**7.2.1　Observation/Examination Schedule**

The survey, observation, and evaluation items, along with the visit schedule for this study, are as follows.

|  | Pre-regist.  ~ Regist. | Surg. Date | PO 1 w | Discharge date | PO 30 d | PO 1y | PO 2 y |  |
| --- | --- | --- | --- | --- | --- | --- | --- | --- |
| Allowed Period |  |  |  |  | Within  ±14d | Within  ±56 d | Within ±56d | |
| Registration/Assignment | ● |  |  |  |  |  |  |  |
| Patient Background Information | ●※1 |  |  |  |  |  |  |  |
| Surgery (Protocol Treatment) |  | ● |  |  |  |  |  | |
| Surgery Information |  | ● |  |  |  |  |  |  |
| Intraoperative Complications/Adverse Events |  | ● |  |  |  |  |  |  |
| Early Postoperative Complications/Adverse Events |  |  |  |  |  |  |  |  |
| Medical History/Physical Examination | ●※1 |  | ● | ● | ● | ● | ● |  |
| JOA score | ●※1 |  |  |  |  | ● | ● |  |
| Cervical Plain X-ray  (Cervical Alignment) | ●※1 |  | ● |  |  | ● | ● |  |
| Cervical Plain CT  (Postoperative: Enlarged Laminar Retention Rate, Hinge Fracture/Bone Union) | ●※1 |  | ● |  |  | ● | ● |  |
| Cervical Plain MRI  (Paraspinal Muscle Cross-sectional Area) | ●※1 |  |  |  |  | ● | ● |  |
| Cervical Plain MRI  (Dural sac Area) | ●※1 |  |  |  |  | ● | ● |  |
| Cervical Plain MRI  (Grading of the mass posterior to the dural sac) |  |  |  |  |  | ● | ● |  |
| Late Postoperative Complications/Adverse Events |  |  |  |  |  |  |  |  |
| Health-Related QoL（EQ-5D） | ●※1 |  |  |  |  | ● | ● |  |
| Pain/Numbness Severity (VAS) | ●※1 |  |  |  |  | ● | ● |  |
| Cervical Disability Index (NDI) | ●※1 |  |  |  |  | ● | ● |  |
| Outcome Follow-up |  |  |  |  |  | ● | ● |  |
| Direct Medical Costs |  |  |  |  |  |  |  |  |

● ：Required

※1 : All surveys, observations, and tests related to this clinical study will be conducted after obtaining written consent from the research subjects. However, results from surveys, observations, tests, etc., performed as part of routine care prior to obtaining consent may be used as research data if they were conducted within 360 days prior to registration.

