| Early Postoperative Complications/Adverse Events (within 30 days postoperatively) | | Confirm the presence of adverse events through medical history and physical examination.  If an adverse event occurs, document the event name, onset time, outcome, severity (including whether reoperation was required), relationship to cervical spine surgery, treatment details/date of treatment, and whether hospitalization was extended. | |
| Medical History/Physical Examination | | Conduct medical history and physical examination during regular postoperative outpatient visits. | |
| Plain X-ray | | Cervical spine (AP/Lateral/Anterior flexion lateral/Posterior flexion lateral): Confirm C2-7 angle/C-SVA/C7 slope  Full spine standing (AP/Lateral): Confirm SVA/Lumbar lordosis angle/Thoracic kyphosis angle/Pelvic incidence, check for existing vertebral fractures | |
| Cervical Plain CT | | Horizontal, sagittal, and coronal slices at each intervertebral level: Confirm presence of OPLL/Lamina retention rate, hinge fractures/gutter bone union. | |
| Cervical Plain MRI | | T2 and T1 sagittal/horizontal images  Preoperative: Maximum stenosis level, presence of intramedullary signal changes, C4/5 paraspinal muscle area, dural sac area  Postoperative: C4/5 paraspinal muscle area, dural sac area, Grading of the mass posterior to the dural sac | |
| Late Postoperative Complications/Adverse Events (From 31 days post-op to within 2 years post-op) | | If an adverse event occurs, document: event name, onset timing, severity, outcome, seriousness (whether reoperation required), relationship to cervical spine surgery, treatment details/date, and hospitalization status. | |
| Outcome Investigation | | Survival (Last confirmed survival date, presence/absence of death, date of death, cause of death)  Reoperation (Reoperation presence/absence, reoperation date, reason for reoperation, reoperation method)  Study Discontinuation (Discontinuation presence/absence, discontinuation date, reason for discontinuation) | |
| Direct Medical Costs | | Hospitalization Costs (Medical fees excluding surgery, surgery-related costs [surgery, surgical drugs, anesthesia, anesthetic drugs])  Outpatient Costs (Consultations, tests, drugs, other)  Hospitalization Re-treatment Costs for Adverse Events (Hospitalization medical fees excluding surgery, surgery-related costs [surgery, surgical drugs, anesthesia, anesthetic drugs])  Research collaborators collect the above costs from medical claims. | |

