The retention rate is calculated for each enlarged lamina identified on CT scans at postoperative 1 and 2 years, following previous reports^7)^ (Figure 4). The mean retention rate is also calculated for each patient.

(8) Proportion of hinge fractures at postoperative 1 and 2 years

(9) Percentage of bone union of gutter at postoperative 1 and 2 years

[Definition]

Using CT images at 1 and 2 years postoperatively, evaluate the presence or absence of hinge fractures (fractures of the groove created in the medial facet joint) and bone union in each enlarged lamina, following previous reports^8)^. Evaluate both on horizontal slices. A fracture is defined as a complete disruption of the cortical bone continuity of the target lamina. and bone union is defined as the formation of even partial bony continuity within the excavated groove region of the target lamina. The level and lateral side of each lamina are recorded.

[figure not shown]
(10) Sagittal alignment of cervical spine at postoperative 1 and 2 years (C-SVA, C2-7 angle, T1 slope)

[Definition]

Cervical spine alignment (C-SVA, C2-7 angle, C7 slope) is measured from plain radiographs at postoperative 1 and 2 years, according to previous reports^7)^ (Figure 5). Note that the C2-7 angle is denoted with a positive (+) sign for lordosis.

(11) Paraspinal muscle cross-sectional area (C4/5 level) at postoperative 1 and 2 years

[figure not shown]
[Definition]

Measure the cross-sectional area of paraspinal muscles (mm^2^) on the C4/5 slice of T2-weighted images according to a previous report^20)^, and calculate the total values for each side (Figure 6).

(a: multifidus, b: cervical semispinalis, c: cervical splenius capitis, d: splenius capitis)

(12) Dural sac cross-sectional area (C3/4, C4/5, C5/6, C6/7 levels) at postoperative 1 and 2 years

[Definition]

Measure the dural canal cross-sectional area (mm^2^) on the T2-weighted horizontal slice at each of the C3/4, C4/5, C5/6, and C6/7 levels, following the method described in a previous report^21)^ (Figure 7).

(13) Grading of the mass posterior to the dural sac at postoperative 1 and 2 years

［Definition］

The classification of posterior dural canal compression on the central slice of the T2 sagittal image is evaluated according to a previous report^22)^ (Figure 7).

[figure not shown]

(14) Incremental Cost-Effectiveness Ratio (ICER)

[Definition]

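### Hinge fracture, a stated safety endpoint, is defined and analysed only on the 1- and 2-year CT, so early fractures that have healed score as absent and the scheduled 1-week reading goes unused

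*Protocol*

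**What the plan says.** Protocol 5.1, rationale (8), gives the endpoint its role: "As a safety endpoint, the proportion of hinge fractures in enlarged laminar segments on CT". Section 8.2 (8) and (9) fixes when it is read: "Using CT images at 1 and 2 years postoperatively, evaluate the presence or absence of hinge fractures". The same paragraph defines the two findings:

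- Fracture: "A fracture is defined as a complete disruption of the cortical bone continuity of the target lamina".
- Union: "bone union is defined as the formation of even partial bony continuity within the excavated groove region of the target lamina".

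Readings are made for each enlarged lamina, with level and side recorded. Section 10.5.3 (8) and (9) compares the percentages at 1 and 2 years between groups, with a confidence interval for the difference and Fisher's exact test. It names no other time point and no cumulative count.

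The imaging plan is wider. The Overview lists "2) Postoperative 1 week: CT". In the 7.2.1 schedule the cervical CT row is marked as required before surgery and at 1 week, 1 year and 2 years, and it is labelled "Postoperative: Enlarged Laminar Retention Rate, Hinge Fracture/Bone Union". Section 7.2.2 lists what is read on CT, without limiting the time: "Confirm presence of OPLL/Lamina retention rate, hinge fractures/gutter bone union".

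For endpoint (9), the rationale in 5.1 describes something narrower than 8.2 does: "the proportion of hinge fractures showing bone union on CT was set as a secondary endpoint".

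**The concern.** A hinge may break at surgery or soon after. If it is first read at 1 year, the observed proportion reflects two processes: how often hinges broke, and how often the cortex had become continuous again. The endpoint is offered as a measure of safety, and sections 3.3 and 4 include safety in what the trial sets out to show for the suture-anchor method. A comparison of late readings alone cannot tell a method that rarely breaks the hinge from one whose broken hinges usually heal.

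The 1-week scan that would separate the two is already required and already labelled for hinge fracture. As written, that reading would be collected and then left out of every planned comparison.

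**Working it through.** The protocol states no hinge-fracture rate, healing rate or power for this endpoint, so there is no figure to reproduce. The sample size in 10.2 (172 evaluable, 216 enrolled) concerns the JOA recovery rate and is unaffected. The check is a comparison of sections, followed by algebra.

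**1. Sections side by side**

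| Place | Times at which hinge fracture is read or used |
|---|---|
| 7.2.1 schedule, CT row labelled for hinge fracture | 1 week, 1 year, 2 years |
| 7.2.2 CT items | hinge fracture listed, no time limit |
| 5.1, 8.1.2 and 8.2, endpoint (8) | 1 and 2 years |
| 10.5.3 (8), analysis | 1 and 2 years |
| 8.2 Tables A, B and D (surgical and late complications) | hinge fracture not named |

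The 1-week hinge reading is foreseen as an observation but appears in no endpoint definition and no analysis. The complication tables do not reliably fill the gap. A fracture without symptoms would enter only if someone recorded it under an unspecific category.

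**2. What the definition does to one hinge**

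- Fractured at 1 week, cortex still completely disrupted at 1 year: scored as fracture.
- Fractured at 1 week, cortex continuous again at 1 year: scored as no fracture.
- Intact at 1 week, broken later and still disrupted at 1 year: scored as fracture.
- Intact at 1 week, broken later and continuous again by 1 year: scored as no fracture, and missed by the 1-week scan too.

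The second line is the point. It follows from the wording of 8.2 and needs no outside fact.

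**3. Effect on a group comparison**

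Let p be the proportion of patients in an arm with an early fracture and h the share of those no longer meeting the definition at 1 year. Leaving later fractures aside, the observed proportion is p(1 − h).

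- Equal h in both arms: the observed difference is (p₁ − p₂)(1 − h), which is always smaller than the early difference.
- Unequal h: the observed difference is p₁(1 − h₁) − p₂(1 − h₂), which can be smaller or larger than the early difference or have the opposite sign.

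All rates below are assumed, to show the range only:

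| Early fracture, arm 1 / arm 2 | Healed by 1 year, arm 1 / arm 2 | Seen at 1 year | Early difference | Difference at 1 year |
|---|---|---|---|---|
| 30% / 10% | 25% / 25% | 22.5% / 7.5% | 20 points | 15 points |
| 30% / 10% | 50% / 50% | 15% / 5% | 20 points | 10 points |
| 30% / 10% | 90% / 90% | 3% / 1% | 20 points | 2 points |
| 20% / 20% | 50% / 90% | 10% / 2% | 0 points | 8 points |

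For the last row, 0.20 × 0.50 = 0.10 and 0.20 × 0.10 = 0.02. The table is per patient, whereas 8.2 reads each lamina, so it illustrates the mechanism and does not forecast a result.

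**4. Endpoint (9)**

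Section 5.1 speaks of union among hinge fractures, so its denominator is fractured hinges. Section 8.2 assesses union in each enlarged lamina, so its denominator is all of them. If fractured hinges are meant, those that had healed by the late scan are missing from a denominator formed on that scan. An earlier reading is needed to find them.

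**The case against.** The strongest reply has four parts.

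- **Fracture still present at 1 or 2 years is a legitimate measure.** It matches the timing of endpoints (3) to (13), and preferring early occurrence is partly a matter of taste. This stands, and it is why the late readings should be kept. It does not explain why a required 1-week reading of a safety finding has no use.
- **The gap is in reporting, not clearly in data capture, and a separate analysis plan could add a 1-week table.** The first half is right. On the second, the protocol itself fixes the endpoint's times in 5.1, 8.1.2, 8.2 and 10.5.3, so the correction belongs there.
- **The consequence is limited.** The only non-inferiority rule, in 10.5.2, concerns the JOA recovery rate. Hinge fracture is one of 15 secondary endpoints and has no margin. Safety is also covered by lamina retention, complications and reoperation. This stands and sets the weight of the point.
- **The definitions do not make endpoint (8) the mirror image of endpoint (9).** A reader might infer that they do, but the documents do not support it. Fracture is defined by the cortex of the lamina and union by bone in the groove. An unfractured hinge with an unfilled groove could be neither, and a partly bridged groove under an interrupted cortex could be both. Scoring follows a cited report that is not at hand. The claim that a healed fracture scores as absent is secure only where the cortex is continuous again.

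**Conclusion.** The point holds as a mismatch within the protocol with a real effect on interpretation. Endpoint (8) misses early hinge fractures whose cortex has become continuous by 1 year, and the 1-week reading that would show those present by then enters no endpoint or analysis. The conclusion rests only on the protocol's definitions and schedule.

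The size is unknown, because it depends on fracture and healing rates that the protocol does not give. A reader might infer that the late reading always shrinks the difference and so favours a finding of no worse safety. That holds only if healing is similar in the two arms. With unequal healing the late reading can create a difference that was not there at the start. For the same reason no loss of power can be stated as a property of this trial.

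The change should be made, but it is not critical: the endpoint is secondary and the primary JOA analysis and sample size do not depend on it.

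**What to change.** - In 5.1, 8.1.2, 8.2 (8) and 10.5.3 (8), add hinge fracture on the 1-week CT, with the same between-group comparison as at 1 and 2 years.
- Label the 1- and 2-year readings as fracture present at that time, whether persistent or new.
- In endpoint (9), reconcile the rationale in 5.1 with the definition in 8.2 by stating the denominator: fractured hinges or all enlarged laminae. If it is fractured hinges, use the 1-week fracture status to identify them.

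The cost is a change of wording and one more item read on scans already required. No imaging is added and the sample size does not change. One limit remains: a fracture that arises after week 1 and heals before 1 year will still be missed, and the text should say so.

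### Hinge fracture, a safety endpoint, is read only on the 1- and 2-year CT, so it mixes fracture occurrence with healing; add by-arm counts from the 1-week CT already scheduled

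*Protocol*

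**What the plan says.** Protocol section 5.1, rationale (8), gives the endpoint a safety role: "As a safety endpoint, the proportion of hinge fractures in enlarged laminar segments on CT". Section 8.2 (8)/(9) fixes the images: "Using CT images at 1 and 2 years postoperatively, evaluate the presence or absence of hinge fractures". It then defines the two readings. For fracture: "A fracture is defined as a complete disruption of the cortical bone continuity of the target lamina". For union: "bone union is defined as the formation of even partial bony continuity within the excavated groove region of the target lamina". Section 10.5.3 (8)/(9) calculates the percentages by group at 1 and 2 years and at no other time.

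The imaging plan is wider. The Overview lists "Postoperative 1 week: CT". In the schedule of section 7.2.1 the plain CT row is marked before surgery and at 1 week, 1 year and 2 years, and its label reads "Postoperative: Enlarged Laminar Retention Rate, Hinge Fracture/Bone Union". Section 7.2.2 gives the CT reading items without tying them to a visit: "Confirm presence of OPLL/Lamina retention rate, hinge fractures/gutter bone union".

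For the companion endpoint (9), rationale (9) in section 5.1 speaks of the share of hinge fractures that show union. Section 8.2 instead assesses union in each enlarged lamina, whether or not it was fractured.

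**The concern.** A hinge can break while the lamina is opened and fixed, or later. The arms differ in how the opened lamina is held, so the safety question includes whether one technique produces more fractures. That is a question of occurrence. A reading first taken at 1 year answers another question: how many hinges are then completely disrupted. The second depends on occurrence and on healing during the year, and healing may itself differ between the techniques.

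The error can run either way. Different fracture rates can look alike once most fractures have bridged, and equal fracture rates can look different if one arm heals better. The scan that would separate the two is already required in every patient, but neither the definition nor the analysis of (8) uses it. Because the objective in section 4 covers safety as well as efficacy, the report should be able to say which of the two it is describing.

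**Working it through.** **1. The sections side by side**

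| Section | What it fixes |
|---|---|
| 5.1, rationale (8) | hinge fracture is a safety endpoint |
| 5.1, rationale (9) | union is assessed among hinge fractures |
| 7.2.1 and Overview | a CT is taken at 1 week, 1 year and 2 years; the row label includes hinge fracture |
| 7.2.2 | hinge fracture is a CT reading item; no visit is named |
| 8.2 (8)/(9) | fracture and union are read at 1 and 2 years, for each enlarged lamina |
| 10.5.3 (8)/(9) | percentages at 1 and 2 years only |

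Two things follow. First, (8) is a prevalence at 1 or 2 years, not a count of fractures that occurred. Second, rationale (9) needs a denominator of fractures, and that is best supplied by fractures identified early. The definition in 8.2 uses all enlarged laminae, so rationale and definition do not match.

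**2. Number per arm for an illustration**

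The protocol states no figure for hinge fracture. Its only relevant number is the sample size for the primary endpoint in section 10.2 (SD 40%, margin 20%, one-sided 0.025, power 0.9). By the normal approximation, n per arm = 2 × (1.960 + 1.282)² × 40² / 20² = 2 × 10.51 × 4 = 84.1, so 85. With the t distribution it is 86 per arm, or 172 in total (power 0.903), which reproduces the plan. Then 172 / 0.8 = 215, or 216 with equal arms. I use 86 evaluable patients per arm below.

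**3. Illustration with assumed rates**

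Let p be the share of patients with a hinge fracture on the 1-week CT and h the share of those that no longer meet the fracture definition at 1 year. The rate visible to endpoint (8) is p × (1 − h). All values of p and h are assumptions, and h is taken as equal in the two arms. Power is for the exact two-sided Fisher test at 0.05.

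| Assumed 1-week rates | h | Visible at 1 year | Difference | Power |
|---|---|---|---|---|
| 10% vs 20% | 0 | 10% vs 20% | 10 points | 0.377 |
| | 50% | 5% vs 10% | 5 points | 0.160 |
| | 80% | 2% vs 4% | 2 points | 0.031 |
| | 90% | 1% vs 2% | 1 point | 0.003 |
| 10% vs 30% | 0 | 10% vs 30% | 20 points | 0.889 |
| | 50% | 5% vs 15% | 10 points | 0.522 |
| | 80% | 2% vs 6% | 4 points | 0.128 |
| | 90% | 1% vs 3% | 2 points | 0.021 |

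**4. The opposite error**

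Now let both arms have 20% at 1 week, but let h be 90% in one arm and 60% in the other. The visible rates are 0.20 × 0.10 = 2% and 0.20 × 0.40 = 8%. That 6-point gap comes wholly from healing, yet it would be reported as a difference in hinge fractures.

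**The case against.** Endpoint (8) is consistent with itself: list, title, definition and analysis all say 1 and 2 years, as for the other imaging endpoints (7) to (13). A fracture still present at 1 or 2 years is a legitimate durable outcome. That stands, and it is why the early count should be added beside the present endpoint and not replace it.

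Three stronger readings are tempting and are not supported.

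- *The 1-week CT is scheduled specifically to look for hinge fractures.* The row label is shared by all postoperative CTs and also names bone union, which can hardly be judged at 1 week. The scan may partly serve as the early reference for the retention rate; the figure defining that rate is not shown. What remains is that the protocol lists hinge fracture as a CT reading and gives the 1-week scan no role in (8).
- *A partly healed fracture necessarily disappears.* Fracture is judged on the cortex of the lamina and union on bone within the groove, and the text does not make them mutually exclusive. A hinge with some bridging but a fully disrupted cortex could be scored as both. Early fractures may be missed; the text does not show that all would be.
- *Early fractures are captured nowhere else.* Tables A to D have no row named for hinge or gutter fracture, but those tables list only complications of special interest. Table B has an Other entry, and complications up to 30 days are tabulated by arm under endpoint (15). One Table B row is also rendered differently in section 9.2, so a lamina-fracture row may have been lost in translation. Still, this route depends on someone reporting the event in an open-label trial. It is not a systematic CT count.

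It can also be said that analysis detail belongs to the statistical analysis plan, which is not shown. That does not answer the point, because sections 8.2 and 10.5.3 positively fix the time points.

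**Conclusion.** The point holds in a limited form. As written, (8) measures hinges that are completely disrupted at 1 or 2 years. It cannot separate fracture occurrence from healing, and early fractures that have regained cortical continuity may go uncounted unless reported ad hoc as complications. Rationale (9) does not match the definition in 8.2.

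The documents do not give the size. The illustration rests on assumed fracture rates, on assumed shares no longer meeting the definition, and on the patient as the unit, whereas 8.2 scores each lamina and side. It shows the direction and possible extent of the distortion, not an expected loss. Nor is power claimed for this endpoint: even with nothing lost, 10% versus 20% would be detected with power of only 0.377. The gain is a clear description of safety by arm, not a well-powered test.

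This is one of fifteen secondary endpoints, and the primary non-inferiority conclusion on the JOA recovery rate is unaffected. The change is worth making because it is cheap and bears on the safety claim.

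**What to change.** - Keep the 1- and 2-year proportions in 8.2 (8) and 10.5.3 (8).
- Add, by arm, the proportion of patients and of laminae with a hinge fracture on the 1-week CT, and on any postoperative CT up to 1 year and up to 2 years.
- State in 8.2 whether one hinge can be scored as both fractured and united on the same scan.
- Settle endpoint (9): either union in every enlarged lamina, as in 8.2, or union among hinges found fractured earlier, as in rationale (9) of 5.1. If both are wanted, name both with their denominators.
- Align 5.1, 7.2.1, 8.2 and 10.5.3, and say in 7.2.1 which readings belong to the 1-week CT.

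The cost is wording in four sections and one more reading of a scan that is already scheduled. No new imaging or visit is needed.
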